## Abstract

The impacts of extreme weather events (EWEs), such as droughts and floods, continue to be felt inequitably and disproportionately, with vulnerable communities experiencing diverse effects. While more is known about the direct impacts of EWEs on the general population, there is limited quantified evidence regarding the indirect socioeconomic impacts of climate-driven EWEs on vulnerable sub-populations such as people living with HIV (PLHIV). Globally, South Africa has the largest number of PLHIV, who by the nature of their medical needs and the stigma around their disease burden, have different vulnerability profiles to the wider population. KwaZulu-Natal province, which recorded the second-highest burden of HIV in South Africa, has been hit hard by recurrent floods in recent years. This study aims to evaluate the social and economic impacts of recent floods on PLHIV in the province and co-develop a priority list of policy interventions that would address and minimise flood impacts among PLHIV. This study involves three objectives, and a combination of qualitative thematic analysis and economic assessment will be applied to investigate the socioeconomic impacts of the recent floods in PLHIV across two rural districts in South Africa. The study will apply a mixed-methods exposed-unexposed approach to assess the impacts of recent floods on PLHIV concerning treatment adherence, healthcare use, out-of-pocket expenses, coping mechanisms, work productivity loss, and other economic losses. An equity impact analysis will be conducted to examine how the socioeconomic impacts of floods are distributed disproportionately within the study sample. A priority list of policy interventions will be co-developed to minimise the impacts of floods using participatory research methods and multi-criteria decision analysis. Using a novel mixed-methods approach, this study contributes to understanding the social and economic impacts of recent floods on PLHIV and co-produces a list of adaptive and mitigation policy interventions to address these impacts.

## Introduction

Climate change is one of the most pressing public health issues that threatens to further widen health, social and economic disparities across and within societies [1–6]. The frequency, intensity and duration of extreme weather events (EWEs), such as droughts, floods, and cold and heat waves, have increased in the last few decades globally [3,4,7,8]. Only in 2024, many parts of the world experienced widespread EWEs, such as extreme heatwaves in the Sahel region of Africa [9], heavy rainfalls and flash floods in Germany and Spain [10,11], cold and heat waves in America [12] and tropical cyclone and floods in southeast Asia [13].

The World Meteorological Organization reported a sevenfold increase in disaster losses from EWEs since the 1970s, with the losses expected to be higher in lower-income countries and regions [14]. The impacts of climate-driven extreme events are extensive and include injuries, premature deaths, the spread of infectious disease, mental health impacts, displacement, disrupted healthcare access, food insecurity, water crisis, and disrupted social and economic stability [3,4,15,16]. Economic losses attributable to EWEs can cause livelihood insecurity, making affected populations reprioritise their livelihood needs. For people with pre-existing health conditions, including people living with HIV (PLHIV), it can eventually result in treatment nonadherence and poorer health outcomes, in addition to other issues such as displacement and poverty [4,7,17].

Climate-driven extreme events and their catastrophic consequences will continue to be distributed inequitably, with vulnerable communities and regions affected diversely [18,19]. While more is known about the consequences of climate-related extreme events on the general population, less attention has been paid to the pathways from climate hazards to poor health outcomes or socioeconomic insecurities for specific population sub-groups [5,14,20]. Vulnerable groups of the population, i.e., groups with characteristics susceptible to EWEs impacts [14,21], include older adults, children, and people with pre-existing health conditions. These sub-populations experience a disproportionate share of EWEs impacts, particularly in low and middle-income countries [20,22–24]. Climate change vulnerabilities are more pronounced across socio-economically marginalised communities and can be linked to gender disparities [22,23,25–27].

There is a dearth of evidence on the social and economic impacts attributable to EWEs (e.g., interruptions to healthcare and productivity losses) across vulnerable groups with pre-existing health conditions, such as people living with HIV (PLHIV), particularly in sub-Saharan Africa [5,14,20]. Like any other part of the world, the impact of climate change poses a significant threat to South Africa, and it is rapidly accelerating [18,28]. The April 2022 floods in KwaZulu-Natal (KZN), South Africa, resulted in more than 400 deaths, severe damage to infrastructure and disruption of services, including healthcare, with over 40,000 people displaced [29,30]. The province was again hit by more storms and flash floods in 2024, which caused further damages to infrastructure, including an estimated number of over 814 households (around 4,297 people) affected and 21 fatalities confirmed in the province [31]. South Africa currently ranks first globally in HIV cases, with an estimated 7.8 million PLHIV accounting for 13% of global HIV cases [32–34], and KZN is widely recognised as the epicentre of the HIV epidemic in South Africa, with an adult HIV prevalence of 30% [35].

Prior studies have investigated the impact of climate change and EWEs on lives and livelihood vulnerabilities using qualitative research approaches [24,25,36,37]. While qualitative research is imperative to reveal and elucidate the EWEs’ hidden impacts and pathways in more breadth and depth [37], quantitative data (e.g., productivity losses or healthcare costs) demonstrates the extent of impacts and allows for assessment of population subgroup differences [38]. There is clearly a need for both quantitative and qualitative methodologies to elucidate the complex, interrelated and multi-dimensional impacts of EWEs on humans.

The S3E study aims to explore and evaluate the economic, social, and health impacts of the recent KZN floods on PLHIV and co-create priority policy interventions to mitigate these impacts. The objectives of the study are to:

Understand the impact of floods on healthcare utilisation, lives and livelihoods amongst PLHIV.Measure economic productivity losses and healthcare costs associated with recent floods in PLHIV.Identify and create a priority list of sustainable and adaptive actions to minimise the health, economic and social impacts of floods on PLHIV.

## Materials and methods

### Study design and setting

The S3E study adopts a mixed-methods design where a mix of qualitative and quantitative data collection techniques will be applied to investigate experiences of PLHIV concerning disrupted access to healthcare, treatment adherence, and coping mechanisms in addition to economic losses (including productivity losses) during the recent floods in South Africa. A retrospective community-based exposed-unexposed approach will be carried out in relation to the first two study objectives.

The study will be implemented in the Hlabisa municipality, where the Africa Health Research Institute (AHRI) hosting the study is located, and the Ndwedwe municipality, iLembe district, both in KZN, South Africa. Fig 1 represents the map of the two study areas. These two municipalities were selected because Hlabisa (i.e., unexposed group) was relatively spared by the floods, whilst Ndwedwe, iLembe (i.e., exposed group) was the second most affected sub-district after the city of Durban. The two sub-districts have been selected for comparison as they have similar sociodemographic profiles; both areas are under-resourced rural and socio-economically disadvantaged, and most people live below the poverty line [39,40]. In both areas, HIV is the leading cause of death in individuals aged 25–64 years [41], and antenatal HIV prevalence exceeds 40% [42].

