#### Objective 1. Understanding the impact of floods on healthcare utilisation, lives and livelihoods (March 2025–September 2025).

To understand the impacts of the floods on PLHIV, we will conduct semi-structured in-depth interviews (IDIs) and focus group discussions (FGDs) across the two study sites. Interview questions will cover topics around how PLHIV make sense of their experience of the April 2022 KZN floods – especially for the unexposed population, while the unexposed population (in Somkhele) will explore participants’ views about the 2022 KZN floods and other floods and EWEs experienced in their contexts. The interviews and FGDs will explore how PLHIV were impacted by the floods, including their health, healthcare access and utilisation and livelihood sustenance. We will also interview key informants from health and health-determining sectors, including the Department of Health, Department of Social Development, and Disaster Management Agency, to gain an understanding of actions or inactions towards mitigating the impact of the floods.

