#### Objective 2. Measuring the economic losses and healthcare related costs (March 2025–December 2025).

We will follow the recommended methods to identify and evaluate the impacts of socioeconomic factors associated with floods and measure the economic impacts and losses, including healthcare utilisation and related costs, attributable to recent floods for a randomly selected sample of PLHIV. The study design, analytical methods and reporting of the findings will follow the Consolidated Health Economic Evaluation Reporting Standards (CHEERS) Statement [43].

We will evaluate the economic burdens of floods in terms of direct and indirect costs (e.g., healthcare resources utilisation and work productivity loss). Individual-level data will be collected via structured questionnaires. A micro-costing approach (including a bottom-up construction of costs) will be employed to estimate costs associated with healthcare utilisation and other economic impacts of floods. The overall costs incurred due to floods will be estimated from a provider perspective (and a patient perspective, where data permits). We also collect socioeconomic and demographic information (e.g., age, gender, employment status, etc) of the study participants.

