### Overview of participant recruitment and inclusion criteria

We will recruit PLHIV in the Hlabisa subdistrict through a randomisation process. Potential participants will be randomly drawn from – and recruited – through the AHRI Health and Demographic Surveillance System (HDSS) [39]. In this programme, triannual household-based surveys are used to collect sociodemographic data from approximately 150,000 people in an 845km^2^ area coupled with annual home-based, point-of-care HIV testing, linked to real-time HIV clinical data and health service utilisation records from all 11 regional primary healthcare clinics that provide HIV care, hospitalisation data at the single district referral hospital, and annually death data carried out through verbal autopsies of all deaths in the catchment area. This research database will be used as a sampling frame to randomly select and invite PLHIV to take part in the study in Hlabisa.

AHRI does not have a similar research infrastructure in Ndwedwe, iLembe district. To identify PLHIV in the community without stigmatising them, we will hold monthly meetings with the community engagement department (CED) at AHRI to engage the health facilities and traditional structures in Ndwedwe as part of the community entry process, trust building and stakeholder engagement. Part of this process will entail a series of road shows and edutainment programmes – led by the CED – encapsulating games and educational talks on climate change and health to sensitise the community about the study. Subsequently, the study team will work closely with community caregivers and community-based organisations who have access to PLHIV to facilitate recruitment. Individuals who are recruited through this process will be informed about the study and offered participation if they meet the eligibility criteria. Although it is logistically easier to recruit PLHIV from healthcare facilities, this will introduce selection bias as it means only PLHIV who are still able to access healthcare facilities will be offered participation in the study, and these individuals may differ from the general population of PLHIV in Ndwedwe.

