Participants will be recruited if (a) they are aged 18 years and over, (b) they were diagnosed with HIV before the April 2022 floods, (c) were on antiretroviral therapy before April 2022, (d) were resident in Ndwedwe (exposed group) or Hlabisa (unexposed group) over a month before and during April 2022, (e) were present for and remember the April 2022 floods (for the exposed group), and (f) they are able to give written consent.

More detailed data regarding the study participants and sample size for each study objective is provided in the following sections.

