#### Objective 2. Measuring the economic losses and healthcare related costs.

Following the recommended methods, we will construct a multi-variate econometric model to identify, understand and measure the impact and extent of socioeconomic impacts of recent floods across PLHIV, adjusting for baseline covariates such as age, gender, etc. We will also conduct a cost analysis to measure the economic burdens of floods in terms of direct and indirect costs in South African Rand (SAR), local currency. The SAR will be then converted to US dollar (USD) using the purchasing power parity (PPP) conversion factor recommended by the World Bank [43,60]. The economic impacts of the floods, in terms of the loss of work productivity, will be estimated using the human capital approach to reflect the value of lost production due to absenteeism and presentism associated with recent floods for PLHIV [61,62]. Both descriptive and inferential statistical analysis will be used for comparison purposes, as well as sub-group analysis across exposed and unexposed groups. Following recommended methods, multiple imputations will be used to deal with missing data [63–65]. We will calculate confidence intervals and undertake simulation, bootstrapping and sensitivity analysis to map and assess the uncertainty in our parameter estimates and the robustness of our findings. We will also undertake an equity impact analysis through subgroup analyses of the economic impacts of floods linked with the socioeconomic and demographic characteristics (e.g., age, gender, wealth quintile, etc) of the study sample across exposed and unexposed groups. Data analysis will be undertaken in STATA 16.

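### Objective 2 defines flood exposure only by municipality, so its between-group estimate mixes flood with site and does not support the word attributable

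*Protocol article*

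**What the plan says.** Under Study design and setting, the article states: "A retrospective community-based exposed-unexposed approach will be carried out in relation to the first two study objectives". Each group is a single municipality: "Hlabisa (i.e., unexposed group) was relatively spared by the floods, whilst Ndwedwe, iLembe (i.e., exposed group) was the second most affected sub-district". The eligibility criteria make this a residence rule; participants must be those who "were resident in Ndwedwe (exposed group) or Hlabisa (unexposed group) over a month before and during April 2022". Exposed participants must also have been present for the April 2022 floods and remember them. No criterion or listed data item records whether a household was itself flooded.

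Comparability rests on general similarity: "The two sub-districts have been selected for comparison as they have similar sociodemographic profiles". The support given is rurality, poverty, HIV as a leading cause of death and antenatal HIV prevalence. No pre-flood level of a study outcome is cited for either site.

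The Objective 2 design text aims at losses and costs "attributable to recent floods for a randomly selected sample of PLHIV". The objective as listed in the Introduction uses the weaker term, associated with. The analysis is a multivariable model, "adjusting for baseline covariates such as age, gender, etc", and the sample size section mentions 1:1 matching.

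For Hlabisa there is a surveillance database with linked clinical records, whose stated role is sampling: "This research database will be used as a sampling frame to randomly select and invite PLHIV to take part in the study in Hlabisa". The article says that Ndwedwe has no similar infrastructure; recruitment there goes through community caregivers and organisations.

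**The concern.** Everyone in the exposed group belongs to one site and everyone in the unexposed group to the other. The exposure term in a between-group model is then the site indicator, and the two cannot be fitted together. Whatever differs between the municipalities as a whole enters the coefficient that will be read as the flood effect. Some of these differences come from the study itself. The surveillance programme operates in Hlabisa only, recruitment is a random draw in one site and community referral in the other, and interviews take place in different kinds of venue.

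The label is also loose. Hlabisa was only relatively spared, and its Objective 1 participants will be asked for their "views about the 2022 KZN floods and other floods and EWEs experienced in their contexts". Eligibility is tied to April 2022, while Objective 2 refers to recent floods and the Introduction also describes floods in 2024.

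At stake is what the study may conclude. A site gap could appear as a flood loss where there is none, or an opposite gap could hide a real one. Enrolling more people in the same two sites makes either error look more certain.

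**Working it through.** **1. The plan's own figure.** Inputs from the Objective 2 sample size section: odds ratio 1.9, significance level 0.05 (two-sided assumed), power 80%, background loss from care 20–30%.

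- At 20% background, the exposed proportion is 1.9 × 0.20 / (1 − 0.20 + 1.9 × 0.20) = 0.38 / 1.18 = 0.322.
- Log-odds-ratio formula: n = (1.96 + 0.842)² × [1/(0.20 × 0.80) + 1/(0.322 × 0.678)] / (ln 1.9)² ≈ 7.85 × 10.83 / 0.412, which gives 207 per group.
- The continuity-corrected two-proportion formula gives 212 per group at a background of 21%.

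So 212 per group is reproduced near the low end of the stated range. The calculation treats the 424 people as independent and allows no variance between sites. The sample size is not in dispute here.

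**2. What the contrast estimates.** Let E be exposure and S the site indicator; by the eligibility rule E = S for every participant. After adjustment for individual covariates:

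expected group difference = flood effect + remaining site gap.

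With two sites and two group means, 2 − 2 = 0 degrees of freedom remain for between-site variation. The data therefore cannot show how large the remaining gap is, and a larger sample in the same sites does not change that.

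**3. Size on a continuous outcome.** Assumptions: a standardised outcome, 212 per group, no flood effect, an unadjusted site gap δ. The document gives no value for δ, so a range is shown.

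SE = √(2/212) = 0.0971 SD. Rejection probability = Φ(δ/SE − 1.96) + Φ(−δ/SE − 1.96).

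| Assumed gap δ (SD) | δ/SE | Probability that a nominal 5% test rejects |
|---|---|---|
| 0.10 | 1.03 | 0.177 |
| 0.15 | 1.54 | 0.339 |
| 0.20 | 2.06 | 0.540 |

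**4. Size on a binary outcome.** The article's 20–30% background range can serve as a scale. It is not presented there as a difference between these sites, and the article says that loss from care will not be estimated, so this too is illustration only. With no flood effect and 212 per group:

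| Background, site A v site B | Odds ratio from site alone | Probability of rejection |
|---|---|---|
| 20% v 25% | 1.33 | 0.23 |
| 25% v 30% | 1.29 | 0.21 |
| 20% v 30% | (0.30/0.70)/(0.20/0.80) = 1.71 | 0.66 |

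The last odds ratio is not far from the 1.9 that the study is sized to detect.

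**5. What the plan has to set against this.**

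- *Matching and covariates* act on measured differences between people. Employment status and wealth can be adjusted for, and so could distance to clinic if recorded. Prices, clinic functioning and the presence of a surveillance programme are shared by a whole site and cannot.
- *Similar sociodemographic profiles* make large gaps less likely, but do not give the pre-flood level of costs, visits or lost work.
- *Surveillance records* could supply a pre-flood level for Hlabisa, but with no counterpart in Ndwedwe they give no two-site baseline.
- *Bootstrapping, imputation and sensitivity analysis* address sampling error and missing data; none, as described, addresses the identity of exposure and site.

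**The case against.** The strongest reply is that much is not visible. The Objective 2 questionnaire is not shown and was to be revised after the qualitative work. A reader might infer that outcomes will certainly be measured after the flood only; the article does not say so, only that no pre-flood contrast is stated. Nor does it say that Hlabisa residents have reported floods, only that they will be asked, or what share of Ndwedwe households was flooded.

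It would also go too far to say that covariates can do nothing. The covariate list is open-ended, 1:1 matching is planned, and the sites were chosen for likeness. These points stand, and they limit the claim to the site-level part of the gap.

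Micro-costing of losses that participants themselves ascribe to the flood does not rest wholly on the site contrast. That stands too, but unexposed participants would then report little by construction, and the comparison group would contribute little to that estimate.

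Finally, a before–after comparison by site is no full cure. It assumes parallel trends between two single sites, and any other shock specific to one site remains confounded with the flood. It also relies on long recall: from April 2022 to fieldwork planned for March–December 2025 is 35 to 44 months, and recall may be better where the flood was more salient. This stands, and it is why that contrast belongs beside the post-flood contrast and is not required as the primary one. None of these replies separates exposure from site.

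**Conclusion.** The concern holds for between-group estimates in Objective 2. As the article describes them, they are aliased with site-level differences that matching and individual adjustment can reduce but not remove, and they do not support the word attributable. The rejection rates of about 18%, 34% and 54% depend on assumed, unadjusted gaps of 0.10–0.20 SD. They show how sensitive the test is to such gaps, not that a gap of that size exists here.

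A reader might also infer that the sample size is wrong or that the comparison is worthless. The documents support neither: the sample size reproduces, and the contrast remains informative as an association. The matter should be settled before the questionnaire is fixed, because no later analysis plan can recover exposure or pre-flood items that were never asked.

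**What to change.** The Data collection section leaves the Objective 2 questionnaire open until the preliminary qualitative analysis is done, followed by a pilot that may revise the model. Within that step:

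1. Ask the same household flood-exposure items at both sites (home damaged, displaced, road or clinic cut off), separately for April 2022 and for later floods. Report an exposure gradient within Ndwedwe, where site is constant.
2. Unless already included, ask about healthcare use, costs, lost work and gaps in antiretroviral treatment in identical form at both sites, for a fixed pre-flood window and an equal post-flood window (for example October 2021–March 2022 and April–September 2022), whether or not the respondent blames the flood. Report the site-by-period contrast alongside the post-flood contrast. State the parallel-trends assumption and the limits of recall over more than three years, and check Hlabisa recall against the linked surveillance records.
3. Describe the two-site contrast as associated with living in the flood-affected area, in line with the objective in the Introduction, and align the term recent floods with the April 2022 eligibility date.

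Cost: a longer interview on top of the 60–90 minutes expected, recall error that may differ by site, and some added variance in the site-by-period estimate. The wording change costs nothing.
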